## Abstract

**Background:**

The implementation of combined radiochemotherapy (RCHT) with temozolomide (TMZ) has lead to a significant increase in overall survival times in patients with Glioblastoma multiforme (GBM), however, outcome still remains unsatisfactory.

The majority of GBMs show an overexpression and/or amplification of the epidermal growth factor receptor (EGFR). Therefore, addition of EGFR-inhibition with cetuximab to the current standard treatment approach with radiotherapy and TMZ seems promising.

**Methods/design:**

GERT is a one-armed single-center phase I/II trial. In a first step, dose-escalation of TMZ from 50 mg/m^2 ^to 75 mg/m^2 ^together with radiotherapy and cetuximab will be performed. Should safety be proven, the phase II trial will be initiated with the standard dose of 75 mg/m^2 ^of TMZ. Cetuximab will be applied in the standard application dose of 400 mg/m^2 ^in week 1, thereafter at a dose of 250 mg/m^2 ^weekly. A total of 46 patients will be included into this phase I/II trial.

Primary endpoints are feasibility and toxicity, secondary endpoints are overall and progression-free survival. An interim analysis will be performed after inclusion of 15 patients into the main study. Patients' enrolment will be performed over a period of 2 years. The observation time will end 2 years after inclusion of the last patient.

**Discussion:**

The goal of this study is to evaluate the safety and efficacy of combined RCHT-immunotherapy with TMZ and cetuximab as first-line treatment for patients with primary GBM.

## Background

Glioblastoma multiforme (GBM) is the most frequent primary malignant brain tumor in adults. Until recently, the standard treatment approach in patients with GBM was neurosurgical resection, as radical as possible, followed by postoperative radiotherapy (RT). However, in spite of technical advances in surgery and radiotherapy, overall survival still remained unsatisfactory with median overall survival times of 9–12 months [1,2].

Over the last decade, a number of clinical investigations on combined radio-chemotherapy (RCHT) after neurosurgical resection have been conducted. A large randomized trial performed by the Neuro-Oncology Working Group of the German Cancer Society evaluated combined RCHT with nimustine plus teniposide versus nimustine plus cytarabine and could obtain a median overall survival time of 16.5 months in patients with GBM [3]. Temozolomide (TMZ), an oral alkylating agent, had demonstrated antitumor activity as a single-agent treatment in recurrent GBM [4-6].

In a pilot phase, the feasibility of concomitant administration of TMZ and fractionated RT followed by 6 cycles of adjuvant TMZ was demonstrated and one could suggest that this combined treatment modality would offer significant benefit for patients with GBM [7]. At the Department of Radiation Oncology at the University of Heidelberg a trial evaluating combined RCHT with TMZ in a dosage of 50 mg/m^2 ^5 days per week was conducted, without adjuvant application of TMZ; we observed a median overall survival time of 19 months, and treatment-related toxicity was low [8].

A large randomized trial conducted by the EORTC evaluated the outcome after combined RCHT with TMZ followed by adjuvant TMZ application as opposed to RT alone; in patients treated with RCHT, overall survival was significantly increased to 14.6 months as compared to RT alone with 12.1 months [9].

Treatment-related toxicity was relatively high in the combined treatment arm with 14% of patients presenting with WHO Grade 3 or 4 hematologic toxicities as compared to 7% in the RT-group. Additionally, RT was interrupted or delayed in 32% of the RCHT-patients, and only 47% of all RCHT patients completed the planned 6 cycles of adjuvant TMZ-application. However, the significant increase in overall survival can be considered a major progress and thus the current standard for patients with GBM is considered RT together with the concomitant and adjuvant application of TMZ.

In spite of these advances in outcome, overall survival is still dissatisfactory. Therefore, novel approaches must be implemented into clinical evaluation. Recently, a number of molecular targeting agents have been developed and evaluated in early clinical trials. The main ulterior motive for these therapies is that by intervening into molecular mechanisms the treatment resistance of cancer cells may be overcome, and an amplification of the RCHT-response might be achieved.

To date, several targets have been identified and include vascular-endothelial growth factor (VEGF), platelet-derived growth factor (PDGF), agents targeting components of the Ras- and Akt-mediated pathways, as well as the human epidermal growth factor receptor (HER). All of these are known to play a key role in tumorigenesis and disease progression [10].

The HER-family consists of four distinct receptors: HER1/EGFR (epidermal growth factor receptor), HER2, HER3 and HER4 [11,12]. The EGFR gene is a proto-oncogene that is often amplified in a variety of human tumors [13,14]. The EGFR-gene is located on chromosome 7 and encodes for a 170 kD transmembrane glycoprotein with intrinsic tyrosine-kinase activity [15,16]. The receptor molecules consist of an extracellular ligand binding domain and an intracellular tyrosine kinase that is activated via conformational change in the intracellular protein domain due to extracellular ligand binding and receptor dimerization; the activation of the tyrosine kinase results in phosphorylation of intracellular substrate proteins, kicking off an intracellular reaction cascade regulating cell function and division, apoptosis, adhesion, motility and neoangiogenesis [17]. There are also several mutant HER1/EGFR, the most common one being EGFRvIII, which is constitutively activated and leads to downstream intracellular cascade activation without ligand binding [18-20].

In GBM, the EGFR gene is one of the most frequently amplified proto-oncogenes; expression of the EGFR-protein has been observed in 24–95% of cases [13,14,21] (Table 1).

The real prognostic significance remains unclear to date. However, in a number of other cancers including breast, bladder, esophagus, cervix, ovary, lung and head and neck the overexpression of EGFR has been reported to be a poor prognostic factor [22-24].

A number of small molecules acting as tyrosine-kinase inhibitors (TKIs) have been evaluated in the treatment of GBM. A subgroup of patients demonstrated a response to these agents, however, no correlation with overall survival could be demonstrated [25,26]. A recent publication by Mellinghoff et al. could identify patients expressing EGFRvIII as well as the tumor suppression protein PTEN showing a greater response to the TKIs [25].

Cetuximab is a monoclonal antibody binding specifically to EGFR and thus inhibiting downstream signal transduction pathways [27]. It has been shown that cetuximab enhances radiosensitivity, promotes radiation-induced apoptosis, decreases cell proliferation, inhibits radiation-induced damage repair and inhibits tumor angiogenesis [23].

A number of clinical studies with the EGFR-antibody cetuximab have shown that its application is efficacious and tolerable, with the most common toxicity being acneiform rash. In general, allergic reactions including anaphylaxis could be a potential side effect. A number of phase I and II clinical studies have been conduced with cetuximab as a single agent and have lead to response rates up to 12% and additional stable disease rates up to 32% of all patients with advanced non small cell lung cancer (NSCLC), ovarian cancer, head and neck cancer and colorectal cancer [23]. A major trial evaluating a combination of radiotherapy plus cetuximab versus radiotherapy alone in patients with locoregionally advanced squamous cell carcinoma of the head-and-neck could demonstrate a significant increase in local tumor control rates as well as in overall survival. In a number of the studies conducted, EGFR-overexpression correlated significantly with patients' outcome [22,23,28,29].

Therefore, two main rationales have lead to the initiation of the present study protocol:

1. Overexpression of EGFR has been shown to influence outcome of EGFR-inhibition in patients with extracranial tumors.

2. The majority of GBM show overexpression of EGFR as wildtype or as mutant.

Therefore, the present study protocol evaluates EGFR-inhibition with cetuximab together with the standard radiochemotherapeutic treatment consisting of RCHT with TMZ for patients with primary GBM.

## Methods/design

### Study design

The study is designed as a one-armed study evaluating the feasibility and toxicity of combined radiochemo-immunotherapy with TMZ and cetuximab. The trial can be divided into two phases: During the Phase I part, dose escalation of TMZ from 50 mg/m^2 ^to 75 mg/m^2 ^together with RT and cetuximab will be performed. Thereafter, the Phase II part of the trial will be initiated with a daily total dose of 75 mg/m^2 ^with concomitant RT and cetuximab.

### Study objectives

Primary endpoint of the study is feasibility and toxicity of combined trimodal therapy with TMZ, cetuximab and radiotherapy. According to the current standard treatment for patients with GBM, about 10% off all patients develop WHO Grade III and IV toxicity [9]. We defined a toxicity rate of 30% for WHO Grade III and IV side effects as overall acceptable for this study.

Secondary endpoints include overall survival, progression-free survival and quality of life.

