### Statistical calculations for trial sample size

The trial is evaluating in its Phase 1 part the tolerability of the TMZ dose of 75 mg/m^2 ^together with cetuximab in a two step escalation with a maximum of 12 patients, while evaluation in its Phase II part the following two hypotheses:

1. non-tolerable toxicity H0: existence of no tolerable toxicity, i.e. TR >30%, NTR ≤70%

2. tolerable toxicity H1: existence of tolerable toxicity, i.e. TR < 10%, NTR ≥90%

with RT denoting the rate of toxicity and NTR the rate of non-toxicity. Therefore, the trial consists of a dose finding part (Phase I) and a feasibility part (Phase II).

These two hypothesis will be examined using a two-step optimal phase II design according to Simon et al. [30] in the defined patient population with a significance level of 5% (alpha = 0.05) and a power of 90% (beta = 0.1) with a one-armed analysis in this single arm trial.

To demonstrate tolerability of the toxicity with a hypothesis-test between NONTOX of 70% versus the anticipated NONTOX of 90% within a One-Step-Phase II Design, 36 evaluable patients are required (NCSS PASS 2000).

We calculated a drop-out rate of 10%, and therefore a projected patient number of 40 is planned.

With inclusion of the 6 patients for the dose-finding part of the protocol, a maximum of 46 patients will be included into the study.

Recruitment will be carried out over 2 years and a follow-up time of 1 year per patient is required to evaluate the primary endpoint.

Overall survival will be determined as the time span between primary diagnosis and death of lost to follow-up (censored observation). Progression-free survival will be determined as the time span between start of the treatment and tumor progression or death, whatever occurred first or an event which characterises a censored observation.

The trial consists of a dose-finding study (part 1; Phase I) followed by a Phase II component.

#### Step 1

3 patients are treated with combined RCHT (RT at dose level 1 (DL1) with a total dose of 60 Gy in 2 Gy single fractions + TMZ 50 mg/m^2^/day, 6 weeks)

Cetuximab (ERBITUX^®^) is applied in a dose of 400 mg/m^2 ^in week 1, thereafter weekly at 250 mg/m^2 ^week during the course of RCHT.

Adjuvant treatment: 6 cycles of TMZ 150 mg/m^2^/day for 5 days, every 28 days (q28d)

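### The benchmark of about 10% toxicity behind H1 contradicts the protocol's own 14% for haematologic toxicity alone, so the 90% power applies to a rate below the backbone's stated floor

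*Protocol article*

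**What the plan says.** The Study objectives section of the protocol article introduces the benchmark for the primary endpoint: with current standard treatment, "about 10% off all patients develop WHO Grade III and IV toxicity [9". The next sentence reads: "We defined a toxicity rate of 30% for WHO Grade III and IV side effects as overall acceptable for this study".

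The Background describes the randomised trial cited as [9], which compared radiotherapy plus temozolomide with radiotherapy alone. It calls toxicity in the combined arm relatively high, with "14% of patients presenting with WHO Grade 3 or 4 hematologic toxicities as compared to 7% in the RT-group".

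The section on sample size sets the null hypothesis as "existence of no tolerable toxicity, i.e. TR >30%, NTR ≤70" (per cent) and the alternative as "existence of tolerable toxicity, i.e. TR < 10%, NTR ≥90" (per cent). It plans a "two-step optimal phase II design according to Simon et al. [30"] "with a significance level of 5% (alpha = 0.05) and a power of 90% (beta = 0.1"). It also names a one-step design needing 36 evaluable patients, raised to 40 for 10% drop-out. The Interim analysis section repeats the alternative as 10% or less and closes the trial if 8 or more grade III/IV toxicities are seen after 15 patients.

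**The concern.** The 10% and the 14% are attributed to the same trial, the same treatment and the same severity grades. The larger figure covers only one class of toxicity and the smaller is presented as the rate for all of it. Both cannot be right as written.

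This matters because the 10% appears to carry the design. No other reason is given for placing the alternative at 10%, and the power is calculated there. The regimen under study adds cetuximab to the backbone. If the backbone alone already exceeds 10%, a regimen to which cetuximab adds no severe toxicity would still fail the tolerability test more often than the planned 1 in 10.

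A smaller matter sits beside it. The objectives call 30% acceptable, whereas the test treats 30% as the boundary that it has to reject.

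**Working it through.** **Inputs.** From the sample-size section: null toxicity rate 30%, alternative 10%, alpha 0.05 (taken as one-sided because the hypotheses are directional), power 90%, 36 evaluable patients. From the Interim analysis section: a look after 15 patients, closing at 8 or more toxic. From the Background: 14% haematologic toxicity. The article prints no final cut-off, so the cut-offs below are re-derived.

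**Formula.** Let t be the true toxicity rate. Stop if s or more of the first 15 patients are toxic. Otherwise enrol 21 more and declare the regimen tolerable if at most c of 36 are toxic. Then

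P(tolerable | t) = Σ over x = 0 to s−1 of P[Bin(15, t) = x] × P[Bin(21, t) ≤ c − x].

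Without an interim look this is P[Bin(36, t) ≤ c].

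**Reproducing the plan's figure.** An exhaustive search for the Simon optimal design (non-toxicity 70% versus 90%, alpha 0.05, power 0.90) gives: stop at 11 or fewer non-toxic of 15 (s = 4), and reject the null at 30 or more non-toxic of 36 (c = 6). Total size is 36, type I error 0.046 and power 0.905. This matches the 36 patients and the 90% power. Drop-out also reproduces: 36 / 0.90 = 40.

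**The same design at t = 14%.**

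| x toxic of 15 | P(x) | P(at most 6 − x of 21) | product |
|---|---|---|---|
| 0 | 0.1041 | 0.9797 | 0.1020 |
| 1 | 0.2542 | 0.9372 | 0.2382 |
| 2 | 0.2897 | 0.8392 | 0.2431 |
| 3 | 0.2044 | 0.6622 | 0.1353 |

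The sum is 0.719. The chance of missing a tolerable verdict is therefore 1 − 0.719 = 28%, against the planned 10%.

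**Other rules with 36 patients.** The re-derived first stage stops at 4 toxic of 15; the article's interim rule stops at 8. With c = 5 or 6, eight toxic patients already exceed the final cut-off, so the written interim rule never changes the verdict and its figures equal the one-step figures.

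| Rule | type I error at 30% | power at 10% | power at 14% | power at 20% (assumed rate) |
|---|---|---|---|---|
| Simon optimal: stop at 4 of 15; at most 6 of 36 | 0.046 | 0.905 | 0.719 | 0.361 |
| Written interim rule or one step; at most 6 of 36 | 0.054 | 0.937 | 0.768 | 0.401 |
| Written interim rule or one step; at most 5 of 36 | 0.022 | 0.855 | 0.609 | 0.246 |

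The middle rule breaches the stated 5%. The last keeps it but falls short of 90% power even at 10%.

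**Scale.** For 90% power at 14% against 30%, an exact one-step design first reaches the target at 57 evaluable patients, and does so at every size from 65 upwards.

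**The case against.** The strongest reply is that H1 is only the point at which power is evaluated. The test has to reject 30%; it does not have to show 10%. Under the re-derived cut-off, 6 toxic of 36 (16.7%) would still pass. That stands. A reader might infer that the trial requires the triple combination to be less toxic than its own backbone, but the hypotheses as tested do not require this. What remains is that the stated power describes a rate below the document's own floor, and that the objectives present 10% as an observed rate, not as a target.

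Second, the 72% belongs to a design whose critical values are not in the article and whose first stage differs from the written interim rule. This also stands, and is why a range is given. Power at 14% is well below 90% under every rule. For the same reason the cut-off of 6 of 36 cannot simply be written in: with the written interim rule its type I error is 0.054.

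Third, a reader might take the sentence calling 30% acceptable to mean that a result such as 7 to 10 toxic of 36 (19% to 28%) is acceptable in one section and a failure in another. The text does not go that far. Thirty per cent as the limit of acceptability for the true rate is largely consistent with the null boundary; the objectives give no rule for observed counts, and failing to reject is inconclusive, not proof of intolerability. The wording is loose rather than contradictory.

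Finally, the 10% might refer to non-haematologic events or to the concomitant phase only. The article does not say so. It counts grade III and IV toxicities without restriction and requires a year of follow-up per patient to evaluate the primary endpoint.

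**Conclusion.** The concern holds in limited form. The benchmark of about 10% contradicts the 14% reported from the same trial, and the 90% power rests on it. At a true rate of 14%, power is about 72% under the design that reproduces the planned size, and 61% to 77% under other rules with 36 patients. The corresponding chance of failing to declare the regimen tolerable is 23% to 39%, against the planned 10%.

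This rests on a one-sided test, on re-derived cut-offs, and on 14% as the lowest rate that the document supports for the backbone. Other severe toxicity, or an effect of cetuximab, could only raise the rate; the article does not give the overall figure, so 20% is an illustration. The sample-size arithmetic is sound for the rates it uses. The benchmark error leaves type I error at 30% unchanged, so it does not raise the risk of accepting a regimen with 30% toxicity. The damage is to the stated power.

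**What to change.** - In Study objectives, correct the benchmark to agree with the Background (at least 14%, haematologic toxicity alone), or state the source and scope of the 10%.
- In the sample-size section, keep the number of patients and both hypothesised rates, but say that 90% power holds only at a true rate of 10% and report the power at 14%. Any higher rate, such as 20%, should be labelled as an assumption.
- In Study objectives, describe 30% as the null boundary that the test must reject.
- State the final cut-off only after the sample-size and Interim analysis sections have been reconciled, since type I error and power both depend on which rule applies.

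The first three changes are to wording. Their cost is a less favourable stated power: about 72% at 14% if the Simon optimal design is the one intended.

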### Trial organization

The study protocol of GERT was designed by the study initiators at the Department of Radiation Oncology at the University of Heidelberg. It is an investigator-initiated trial (IIT); trial medication is provided by Merck KgaA in Darmstadt, Germany. The trial is conducted at the Department of Radiation Oncology at the University of Heidelberg.

### Coordination

The overall coordination is performed by the Department of Radiation Oncology at the University of Heidelberg, and this department is responsible for overall trial management, trial registration, database management and quality assurance. The study monitoring according to the guidelines of Good Clinical Practice (GCP) is performed by the Koordinierungszentrum für Klinische Studien (KKS), University of Heidelberg. Biometrical data analysis is conducted together with the Department of Biostatistics of the German Cancer Research Center (dkfz).

### Investigators

The study investigators are experienced radiation oncologists specialized in the treatment of patients with GBM. Patients will be recruited and treated by the physicians of the Department of Radiation Oncology of the University of Heidelberg.

### Patient selection

Inclusion criteria into the study protocol include:

- patients ≥18 and < 70 years of age

- Karnofsky Performance Score ≥60

- histologically confirmed supratentorial GBM

- interval between primary diagnosis and registration for the study < 4 weeks

- patients will be included according to the incidental gender distribution for patients with GBM of ♀/♂ 2:3

- adequate blood values (not older than 14 days prior to initiation of RCHT)

- neutrophil count (ANC) ≥1500/mm3 or white blood cells (WBC) ≥2000/mm3

- platelets ≥100.000/mm3

- hemoglobin ≥10 g/dL

- BUN <1.5 times the upper range

- Total and direct bilirubin <1.5 times the upper laboratory limit

- Adequate liver enzymes <3 times the upper laboratory limit

- Life expectancy >12 weeks

- Written informed consent

Additionally, the combined treatment with radiotherapy and TMZ would be the standard treatment recommended to be performed in the patients included into the study.

### Exclusion criteria

• refusal of the patients to take part in the study

• previous radiotherapy of the brain or chemotherapy with DTIC or TMZ

• known allergy against extrinsical proteins

• previous chemotherapy or therapy with an EGFR-inhibitor

• Previous antibody therapy

• Patients who have not yet recovered from acute toxicities of prior therapies

• Acute infections requiring systemic application of antibiotics

• Frequent vomiting or a medical condition preventing the oral application of TMZ

• Clinically active kidney-liver or cardiac disease

• Known carcinoma < 5 years ago (excluding Carcinoma in situ of the cervix, basal cell carcinoma, squamous cell carcinoma of the skin)

• HIV

• Pregnant or lactating women

• Participation in another clinical study

### Statistical calculations for trial sample size

The trial is evaluating in its Phase 1 part the tolerability of the TMZ dose of 75 mg/m^2 ^together with cetuximab in a two step escalation with a maximum of 12 patients, while evaluation in its Phase II part the following two hypotheses:

1. non-tolerable toxicity H0: existence of no tolerable toxicity, i.e. TR >30%, NTR ≤70%

2. tolerable toxicity H1: existence of tolerable toxicity, i.e. TR < 10%, NTR ≥90%

with RT denoting the rate of toxicity and NTR the rate of non-toxicity. Therefore, the trial consists of a dose finding part (Phase I) and a feasibility part (Phase II).

These two hypothesis will be examined using a two-step optimal phase II design according to Simon et al. [30] in the defined patient population with a significance level of 5% (alpha = 0.05) and a power of 90% (beta = 0.1) with a one-armed analysis in this single arm trial.

To demonstrate tolerability of the toxicity with a hypothesis-test between NONTOX of 70% versus the anticipated NONTOX of 90% within a One-Step-Phase II Design, 36 evaluable patients are required (NCSS PASS 2000).

We calculated a drop-out rate of 10%, and therefore a projected patient number of 40 is planned.

With inclusion of the 6 patients for the dose-finding part of the protocol, a maximum of 46 patients will be included into the study.

Recruitment will be carried out over 2 years and a follow-up time of 1 year per patient is required to evaluate the primary endpoint.

Overall survival will be determined as the time span between primary diagnosis and death of lost to follow-up (censored observation). Progression-free survival will be determined as the time span between start of the treatment and tumor progression or death, whatever occurred first or an event which characterises a censored observation.

The trial consists of a dose-finding study (part 1; Phase I) followed by a Phase II component.

#### Step 1

3 patients are treated with combined RCHT (RT at dose level 1 (DL1) with a total dose of 60 Gy in 2 Gy single fractions + TMZ 50 mg/m^2^/day, 6 weeks)

Cetuximab (ERBITUX^®^) is applied in a dose of 400 mg/m^2 ^in week 1, thereafter weekly at 250 mg/m^2 ^week during the course of RCHT.

Adjuvant treatment: 6 cycles of TMZ 150 mg/m^2^/day for 5 days, every 28 days (q28d)

If 2 out of 3 patients develop DLT, the study will be stopped. If 1 out of 3 patients develops DLT, three more patients will be included at a dose of 50 mg/m^2 ^TMZ. Dose escalation is halted if two ore more patients develop DLT.

#### Step 2

3 Patients are treated with combined RCHT (RT with GD 60 Gy, ED 2.0 Gy + TMZ 75 mg/m^2^/day, 6 weeks)

Cetuximab (ERBITUX^®^) 400 mg/m^2 ^in week 1, thereafter at a dose of 250 mg/m^2 ^weekly during RCHT.

Adjuvant treatment: 6 cycles of TMZ 150 mg/m^2^/day for 5 days, every 28 days (q28d).

If DLT occurs in one patient additional three patients will be treated at DL 2. If 2 or more patients develop DLT, DL 1 will be the recommended dose for the phase II part of the study the study.

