### Interim analysis

An interim analysis is planned after inclusion of 15 patients into the main study. The trial can be stopped should it be obvious that the alternative hypothesis of a tolerable toxicity rate

H1:R≤10% i.e. NONTOX-Rate ≥90%

cannot be achieved, i.e. should the number of WHO grade III and IV toxicities be larger than 7 (meaning 8 or more Grade III and IV toxicities). In this case the study will be closed due to "futility".

Recruitment for the study will be conducted during a period of 2 years. Final evaluation of the primary and secondary endpoints of the study will be performed 1 year after inclusion of the last patient.

The formal end of the study is defined as the end of the observation period of the last patient included into the study.

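### The 36 evaluable patients are a Simon two-step size labelled One-Step, and with the interim rule as written no final cut-off at 36 meets both alpha 5% and power 90%

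*Protocol article*

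**What the plan says.** All statements are in the protocol article.

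- **Hypotheses** (Statistical calculations for trial sample size). The null is "existence of no tolerable toxicity, i.e. TR >30%, NTR ≤70" percent; the alternative is "existence of tolerable toxicity, i.e. TR < 10%, NTR ≥90" percent.
- **Design and error rates** (same section). "These two hypothesis will be examined using a two-step optimal phase II design", "with a significance level of 5% (alpha = 0.05) and a power of 90% (beta = 0.1").
- **Sample size** (same section, next paragraph). For the same 70% against 90% comparison, "within a One-Step-Phase II Design, 36 evaluable patients are required (NCSS PASS 2000").
- **Drop-out** (same section). "We calculated a drop-out rate of 10%, and therefore a projected patient number of 40 is planned".
- **Interim** (Interim analysis). "An interim analysis is planned after inclusion of 15 patients into the main study". The trial may be closed for futility if more than seven grade III and IV toxicities have occurred by then, that is, eight or more.

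The article prints no final cut-off. A condensed article commonly leaves that to the full protocol, and its absence is not part of this point.

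**The concern.** Consecutive paragraphs give two designs for one primary test. The difference matters because a Simon design gets its alpha and power from both of its boundaries together. If the first-stage boundary is replaced by a much looser one, the total of 36 no longer carries the same error rates.

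At stake is whether the stated 5% and 90% describe the test that will be run. They also govern the primary conclusion: whether 6 toxic patients among 36 is compatible with a 5% test depends on which design applies.

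**Working it through.** **Inputs.** Non-toxicity is 0.70 under the null and 0.90 under the alternative, so toxicity is 0.30 and 0.10. Alpha is 0.05, power 0.90, evaluable total 36 and interim size 15, all from the two sections above. Two assumptions are mine. The article does not state sidedness, so one-sided is taken, as is usual for a single-arm phase II test. Each patient counts as toxic or not, so that 8 toxicities means 8 toxic patients. X is the number of toxic patients.

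**Step 1: reproduce the plan's figures.** An exact search over Simon two-stage designs for these inputs returns, as the optimal design, 11/15 and 29/36. It goes on only with 12 or more non-toxic of 15 (3 or fewer toxic) and declares tolerability with 30 or more non-toxic of 36 (6 or fewer toxic). Its alpha is 0.0464 and its power 0.9054. The probability of stopping early under the null is 0.703, so the expected size is 15 + (1 − 0.703) × 21 ≈ 21.2. This reproduces both the 36 and the interim size of 15. The drop-out step also reproduces: 36/0.9 = 40, and 40 + 6 = 46.

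**Step 2: take the One-Step label literally.** For a cut-off c, alpha = P(X ≤ c | n, 0.30) and power = P(X ≤ c | n, 0.10), both exact binomial.

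| n | toxic allowed | alpha | power |
|---|---|---|---|
| 36 | 5 | 2.16% | 85.5% |
| 36 | 6 | 5.36% | 93.7% |
| 37 | 6 | 4.40% | 92.9% |

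At 36, fewer than 5 toxic lowers the power further and more than 6 raises alpha further, so no cut-off meets both targets. The smallest one-step n that does is 37. Reading the 5% as two-sided (upper tail 2.5%) does not help: 5 toxic remains the cut-off, since 2.16% is below 2.5%, and the power is still 85.5%.

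Other one-step formulas do not give 36 either. The one-sided normal approximation is [(1.645 × √(0.7 × 0.3) + 1.282 × √(0.9 × 0.1)) / 0.2]² = 32.4, that is 33. With continuity correction it is 38, by arcsine 33, and two-sided 42.

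**Step 3: apply the interim rule as written.** Stopping requires X ≥ 8 among the first 15.

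- Under the null it stops with probability 0.050, against 0.703 for Simon's first stage.
- Under the alternative it stops with probability 0.00003.
- A trial with 8 toxic patients at the interim cannot finish with 6 or fewer. The rule therefore never removes a trial that would have succeeded at either cut-off, and the final error rates are exactly those of the one-step test: 5 allowed gives 2.16% and 85.5%; 6 allowed gives 5.36% and 93.7%.

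Simon's first stage is what brings the 6-toxic cut-off from 5.36% down to 4.64%, at the price of power falling from 93.7% to 90.5%. The written interim rule does not do this.

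**The case against.** The strongest reply is that this is one wrong word. The 5% and 90% stand in the two-step sentence, not the One-Step sentence, and the two-step design reproduces both 36 and 15. On that reading the sample size is right, and 85.5% belongs to a design nobody intended. The first part stands: 36 is not a wrong number. The second part would settle the matter only if the interim section carried Simon's first-stage boundary. It carries another, so the plan as a whole does not have that design's error rates.

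A second reply is that the size is trivial. The alpha excess with 6 allowed is 0.36 points, a one-step design is one patient short, and the normal approximation asks for only 33. If all 40 planned patients proved evaluable, a one-step cut-off of 6 would give alpha 2.4% and power 90.05%. All of this is correct and limits the weight of the point. It does not make the stated pair true at the 36 evaluable patients on which the plan is based.

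A reader might infer that the trial is underpowered or needs more patients. The documents do not support this. The 85.5% arises only if the test is effectively one-step and alpha is held strictly at 5%; with 6 allowed, power exceeds 90%. Nor does the comparison show that the written interim rule is the wrong one to apply. It shows only that it does not belong to the design named in the sample-size section.

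**Conclusion.** The point holds as an inconsistency between the named design, the One-Step label and the interim rule. Together they leave the stated alpha and power of the primary test undelivered. As written, the test at 36 evaluable patients has either alpha 2.16% with power 85.5% (about 4.5 points below target) or alpha 5.36% with power 93.7% (0.36 points above target). Under Simon's optimal design with its own first stage, the same 36 give 4.64% and 90.5%.

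This rests on exact binomial calculation, toxicity rates of 30% and 10%, one outcome per patient and exactly 36 evaluable. The power of 85.5% is the same under a one-sided or two-sided reading of the 5%. The numerical departure is small, but it concerns the primary test and is cheap to correct.

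**What to change.** Reconcile the sample-size section and the Interim analysis section to one named design, with interim and final boundaries that belong together, and print its exact alpha and power.

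- If the Simon optimal design is meant, delete the One-Step label, resolve the conflict with the written interim rule, and state 4.64% and 90.5%. The total of 36 stands.
- If the test is effectively one-step at 36 evaluable, restate its properties as power 85.5% at alpha 2.2%, or alpha 5.4% at power 93.7%, according to the final cut-off.

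Neither route adds patients. Only a one-step design meant to meet both targets strictly would need 37 evaluable: 37/0.9 = 41.1, so 42 enrolled, and 48 with the 6 phase I patients, against the stated 40 and 46.

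The cost is mostly in the text, but it is not wording alone if the interim boundary changes. Moving from the written rule to Simon's first stage would raise the chance of stopping from 5.0% to 70.3% at 30% toxicity, and from almost nil to 5.6% at 10%. That would change how the study is conducted, and which boundary applies is for the sponsor to decide.
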